#### Ancillary outcome

Medico-economic impact of the program for centers and patients. The cost effectiveness of the program will be assessed by comparing the full costs of implementing and operating the SPEP in the intervention centers to the costs in the control group, and relating the cost difference to the difference in health outcomes. The cost for the healthcare system will be estimated from the total cancer-related costs over the follow-up period (primary time horizon = 1 year, secondary time horizon = 5 years). The analysis will follow the French Health Authority and the Consolidated Health Economic Evaluation Reporting Standards (CHEERS) guidelines on economic evaluation in health care [15, 16]. Hospital costs will be calculated as the diagnosis related group-specific costs weighted by the actual patients’ length of stay. Data collection for out of hospital resources will focus on targeted therapies that represent the highest cost item. The economic evaluation of SPEP compared to adapted physical activity will be expressed as the incremental cost-effectiveness ratio in euro (€) per quality-adjusted life year. We will present the costs differences from the perspective of the health care in the primary analysis and from the perspective of the patients in the secondary analysis. The 95% confidence interval will be estimated by bootstrap method. We will compare the incremental cost-effectiveness ratio to the usually applied thresholds of €50,000–100,000 per quality-adjusted life year and calculate the probability of cost-effectiveness from the bootstrapped probabilistic sensitivity analysis.

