#### Secondary outcomes

Progression free survival is defined as the time from randomization to date of disease progression or death of any cause, whichever occurs first.

Overall survival is defined as the time from the date of randomization to date death of any cause.

Toxicity of the targeted therapy will be assessed using the NCI-CTCAE v4.03. Data concerning the class, frequency, and severity of adverse events will be collected and analyzed. The data will be collected at baseline, monthly during the 3-month program, then every 3 months during the first year of follow-up.

Adherence to targeted therapy will be evaluated by the Morisky-Green questionnaire at baseline then monthly during the 3-month program. This questionnaire, composed of six items related to patient’s adherence to the scheduled treatment, is regularly used to evaluate adherence to oral therapies. Scoring is performed through sum of item scores. Higher scores indicate better adherence to treatment.

For the outcomes described below, patients will fill the French versions of the specific questionnaires at baseline, monthly during the 3-month program, then every 3 months during the first year of follow-up, otherwise indicated. For each questionnaire but EQ-5D-3L, scoring is performed through a simple sum of item scores using the scoring recommendations of the authors.

Quality of life (QoL) will be assessed using the FACT-G and the 3-level version of EuroQol-5D (EQ-5D-3L) questionnaires. FACT-G is composed of 27 items related to patient’s general well-being grouped into four well-being subscales: physical, social/family, emotional, and functional. One score is generated for each subscale and a global QoL score is generated from all items corresponding to the total FACT-G score. For each dimension, a higher score represents a better QoL level. EQ-5D-3L consists of a patient self-rate health on a visual analogue scale (VAS) plus a descriptive system of five dimensions: mobility, self-care, usual activities, pain/discomfort, and anxiety/depression. Each dimension has three levels of perceived problems. Patient decision results into a 1-digit number for each dimension that can be combined into a 5-digit number that describes the patient’s health state.

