**CLINICAL EXAMINATION**						
Observance of oral targeted therapy^b^	●	●	●	●	●^c^	
Medical history and comorbidities	●					
Toxicities related to targeted therapy^d^	●	●	●	●	Every 3 months	
Adverse events related to physical activity^d^		●	●	●		
Clinical examination & vital signs^e^	●	●	●	●	Every 3 months	Every 3 months^k^
Survival Status		●	●	●	Every 3 months	Every 3 months^k^

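### Health-system cost is limited to undefined cancer-related costs while the QALY counts health loss from any cause, so care for exercise-related harm may go uncosted

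*Protocol article*

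**What the plan says.** All of the costing rules stand in one paragraph of the protocol article, under Ancillary outcome.

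- **Scope of the health-system cost:** "The cost for the healthcare system will be estimated from the total cancer-related costs over the follow-up period". The horizon is 1 year for the primary analysis and 5 years for the secondary. The paragraph does not say which costs count as cancer-related.
- **Programme cost:** the evaluation works by "comparing the full costs of implementing and operating the SPEP in the intervention centers to the costs in the control group".
- **Hospital stays:** "Hospital costs will be calculated as the diagnosis related group-specific costs weighted by the actual" length of stay. This sentence sets no limit by cause.
- **Care outside hospital:** "Data collection for out of hospital resources will focus on targeted therapies that represent the highest cost item".
- **Result:** "expressed as the incremental cost-effectiveness ratio in euro (€) per quality-adjusted life year", taken "from the perspective of the health care in the primary analysis", and compared with thresholds of €50,000-100,000 per QALY.

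The only utility instrument described (Secondary outcomes) is the EQ-5D-3L, with the dimensions "mobility, self-care, usual activities, pain/discomfort, and anxiety/depression". Its use for the QALY is implied, not stated.

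Table 1 has a row "Adverse events related to physical activity", marked at M1, M2 and M3 and blank for both follow-up periods. It is separate from the row for targeted-therapy toxicities. Nothing links it to the cost analysis.

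**The concern.** The two halves of the ratio do not have the same scope. The cost is restricted by cause and the effect is not. If a patient falls during an exercise session and is admitted, the EQ-5D-3L registers the loss of mobility and the pain. Whether the admission is costed depends on whether someone classes it as cancer-related. That term is undefined, and the trial is open.

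The cost of treating harm caused by an intervention belongs to its incremental cost. The protocol itself expects that exercise may do harm. It excludes patients with known fracture risk or symptomatic cardiac insufficiency, asks for vital-sign checks before exercise, and records activity-related events. Planned exposure also differs between arms: 12 supervised plus 24 non-supervised sessions under SPEP, against a booklet from which controls choose their exercises. An excess of events under SPEP is therefore plausible, though not certain. If the QALY gain is small, even a modest omitted cost per patient becomes a sizeable amount per QALY.

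**Working it through.** The document gives no expected cost, QALY difference or injury rate, so there is no figure of the plan's own to reproduce. The check has two parts.

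**1. Does the text leave this care out?** Three sentences bear on it.

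- The scope sentence restricts the health-system cost to what is cancer-related.
- The hospital sentence has no restriction by cause. It says how stays are valued, and it follows a sentence that has already set the scope, so it does not clearly widen that scope.
- The phrase on implementing and operating SPEP most naturally means delivering the programme. It neither names nor excludes later care for injuries.

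Exclusion is thus the literal reading, but it is nowhere stated. The narrowing is more explicit for care outside hospital, where data collection centres on targeted therapies.

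**2. What would an omission do to the ratio?** Let p₁ and p₀ be the proportions of SPEP and control patients with one uncosted exercise-related stay, c the cost per stay, and ΔQ the QALY gain, taken as positive.

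Omitted incremental cost per patient = (p₁ − p₀) × c

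Understatement of the ratio = (p₁ − p₀) × c / ΔQ

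Only the excess p₁ − p₀ enters. If it is zero the ratio does not move. If it is negative, the omission works against SPEP.

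Every input below is an assumption: excess 1-5%, €3,000-10,000 per stay, ΔQ 0.01-0.05.

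| Case | Excess × cost per stay | Omitted per SPEP patient | ΔQ | Understatement per QALY |
|---|---|---|---|---|
| Low | 0.01 × €3,000 | €30 | 0.05 | €600 |
| Mid | 0.02 × €6,000 | €120 | 0.02 | €6,000 |
| High | 0.05 × €10,000 | €500 | 0.01 | €50,000 |

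The QALY gain matters as much as the cost. An omitted €300 (0.05 × €6,000) gives €6,000, €15,000 or €30,000 per QALY at gains of 0.05, 0.02 and 0.01. The result is large only when the excess and the cost per stay are high and the QALY gain is very small.

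**The case against.** The strongest reply is that this is one paragraph of a journal article on an ancillary outcome. The list of cost items, and what counts as cancer-related, would normally stand in the full protocol or an economic analysis plan. The paragraph also commits the analysis to French Health Authority and CHEERS guidelines, which are not at hand and may settle how harms are costed. The missing definition alone would therefore be no finding. What remains is that the article does state a restriction by cause, and sets it beside an effect measure that has none.

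A reader might go further and infer that hospital care for exercise injuries is left out and that the ratio therefore flatters SPEP. The document does not support either step.

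- No sentence excludes such care, and some events, such as a fracture at a bone metastasis, could well be classed as cancer-related.
- The rule covers both arms, and controls also receive exercise proposals. Supervision could prevent injuries, or exercise could reduce other admissions. In either case the restriction could work against SPEP.
- The safeguards in the protocol (eligibility limits, intensity adjusted to fatigue, checks before exercise) make a large excess less likely.

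Nor can one say that the comparison with the thresholds would change side, because no expected ratio is given. These objections stand. They limit the point to a possible bias of unknown size and conditional direction.

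**Conclusion.** The concern holds in a conditional form. As worded, the cost side may omit hospital care for exercise-related adverse events while the QALY side counts their effect. If such stays are more frequent under SPEP, the ratio is understated. If they are not, there is no bias in its favour.

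On assumed inputs the understatement lies anywhere from negligible to the size of the lower threshold, and the mid case is small beside that threshold. The document cannot narrow this range. The conclusion also assumes that the EQ-5D-3L supplies the utilities. Severity is minor: feasibility, FACT-F and physical well-being are untouched.

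**What to change.** In the Ancillary outcome paragraph:

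1. State that the health-system cost includes, in both arms, hospital stays for physical-activity-related adverse events.
2. Report all-cause hospital cost over the horizon, at least as a sensitivity analysis.

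The first step uses events already recorded at M1-M3 and the diagnosis-group costing already planned. On its own it has two weaknesses. Attributing a stay to physical activity is itself an unblinded judgement, and the events are scheduled only to M3 while the primary horizon is 1 year. All-cause cost needs no attribution, covers the time after M3, and would equally credit SPEP with any admissions that exercise prevents.

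The price is small: the same costing method applied to more stays, with somewhat noisier all-cause costs and so a wider bootstrap interval for that analysis.

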### Study visits

Patients will be monitored from the date of their randomization until the date of death, withdrawal of consent, or loss to follow-up. The investigators will perform checkup (C) while the coaches will perform evaluation (E). Before any physical exercise, the coach has to monitor patient’s resting pulse rate, oxygen saturation, and blood pressure. Table 1 details the examinations and visits schedule.

**Table 1 Tab1:** Examinations and visits schedule

	Baseline	Physical activity program period			Follow-up 1 (1st year)	Follow-up 2 (5 last years)^a^
		M1	M2	M3		
Inform Consent form	●					
**CLINICAL EXAMINATION**						
Observance of oral targeted therapy^b^	●	●	●	●	●^c^	
Medical history and comorbidities	●					
Toxicities related to targeted therapy^d^	●	●	●	●	Every 3 months	
Adverse events related to physical activity^d^		●	●	●		
Clinical examination & vital signs^e^	●	●	●	●	Every 3 months	Every 3 months^k^
Survival Status		●	●	●	Every 3 months	Every 3 months^k^
**QUESTIONAIRES**						
General QoL (FACT-G, EQ-5D-3L)^f^	●	●	●	●	Every 3 months	
Fatigue (FACT-F)^f^	●	●	●	●	Every 3 months	
Nutrition (FAACT module AC/S)	●	●	●	●	Every 3 months	
Cognitive Function (FACT-Cog)	●	●	●	●	Every 3 months	
Food intake VAS	●			●		
Pain and fatigue VAS	●	●^g^	●^g^	●^g^	Every 3 months	
Adherence to targeted therapy (Morisky-Green)	●	●	●	●		
Anxiety and Depression (HADS)	●	●	●	●		
Daily physical activity						
○ IPAQ	●			●	Every 3 months	
○ Booklet		●	●	●		
○ Questionning about the continuation of physical activity					Every 3 months	
**OTHER ASSESSMENTS**						
Muscle mass, muscle density, adipose tissue (VAT and SCAT), Evaluation (TAP-CT)	●			●	●^h^	
Physical capacities^i^	E0	E1	E2	E3		
**PARACLINICAL EXAMINATIONS**						
Tumor evaluation^j^	●			●	●^l^	●^k, l^
Scintigraphy	●			●	●	
MRI	●			●	●	
**BIOLOGICAL TEST**						
Biological Assessment^k^	●	●	●	●		
**INTERVENTION**						
**Experimental Arm** SPEP Program		Weekly: - 1 supervised SPEP session at the patient’s home - 2 non-supervised sessions				
**TRANSLATIONAL RESEARCH**						
Blood samples^m^	●			●		

*A/CS* Anorexia/cachexia subscale, *ALAT* Alanine transaminase, *ASAT* Aspartate transaminase, *ALP* Alkaline phosphatase, *aPTT* Partial thromboplastin time, *Ca* Calcium, *CBC* Complete blood count, *CRP* C-reactive protein, *E* Evaluation, *EQ-5D-3L* EuroQol-5 dimensions-3 levels, *FAACT* Functional assessment of anorexia/cachexia therapy, *FACT-Cog* Functional assessment of cancer therapy-cognitive, *FACT-F* Functional assessment of cancer therapy-fatigue, *FACT-G* Functional assessment of cancer therapy-general, *γGT* Gamma glutamyl transpeptidase, *HADS* Hospital anxiety and depression scale, *HDL* High-density lipoprotein, *IPAQ* International physical activity questionnaire, *K* Potassium, *LDL* low-density lipoprotein, *M* Month, *Na* Sodium, *NCI-CTCAE* National cancer institute - common terminology criteria for adverse events, *PT/INR* Prothrombin time and international normalized ratio, *PWB* Physical Well Being, *QoL* Quality of life, *SCAT* Sub-cutaneous adipose tissue, *SPEP* Supervised physical exercise program, *T4* Thyroxine, *TAP-CT* Computed tomography of thorax, abdomen and pelvis, *TP* Prothrombin, *TSH* thyroid-stimulating hormone, *VAS* Visual analogue scale, *VAT* Visceral adipose tissue

^a^Every 3 months until disease progression (Tumor assessment according to standard procedures in centers). After progression, the survival status will be evaluated every 3 months until the end of the follow-up period or death

^b^Using the Morisky-Green questionnaire

^c^Until disease progression, death, toxicities, or patient/ investigator decision

^d^Using the NCI-CTCAE V4.03

^e^Pulse rate, blood pressure, temperature, weight

^f^The co-primary endpoint criteria are the fatigue scores (FACT-F) and the physical dimension scores (FACT-G – PWB) evaluated after 3 months

^g^Every week before and after SPEP for Arm A, once a week for Arm B

^h^Scanner at baseline, at 3 months (during the physical activity phase), and at the first follow-up visit (at 6 months after initiation of the physical activity for the SPEP group and 6 months after randomization for the standard group)

^i^The 6-min walking test, muscle force and function, pulse rate, height, weight, body surface area

^j^Tomodensitometry

^k^Hematology (CBC and platelet count), coagulation profile (PT/INR and aPTT), ionogram (NA, K, and Ca), lipid profile (cholesterol total, HDL, HDL, and triglycerides), kidney functions (bilirubin [total, direct, and indirect], ALAT, ASAT, γGT, and ALP), kidney functions (creatinine, creatinine clearance), albumin, thyroid (TSH, T4), CRP

^l^According to standard of care in the center, with an evaluation during the first visit (6 months ±15 days from SPEP initiation [Arm A] or randomization [Arm B])

^m^C-Peptide, Insulin Growth Factor 1, insulin, estradiol, and leptin

#### Inclusion (baseline) visit

Eligible patients with signed informed consent form will have baseline visit at the hospital. Baseline checkup and evaluation will be performed the same day before patient randomization.

Checkup (C0):
Clinical examinationsParaclinical examinationsBiological testsQuestionnaires: VAS (fatigue, pain, and food intake), FACT-G, FACT-F, FACT-Cog, EQ-5D-3L, FAACT-AC/S, and HADSBlood samples for translational research (if consented)

Evaluation (E0):
Physical capacitiesQuestionnaires: VAS (fatigue and pain) and IPAQ

#### Interventional visits

During the intervention phase, the investigator and coach will perform the following checkups and evaluations:
➢ C1 and E1: 1 month ±3 days from SPEP initiation [experimental arm] or randomization [control arm]➢ C2 and E2: 2 months ±3 days from SPEP initiation [experimental arm] or randomization [control arm]

Monthly checkup and evaluation will be performed during the same day for each visit.

Monthly checkup (C1, C2): At the hospital, for all patients.
Clinical examinationsBiological testsQuestionnaires: VAS (fatigue and pain), FACT-G, FACT-F, FACT-Cog, EQ-5D-3L, FAACT-AC/S, and HADS

Weekly evaluations: At home, for patients in the experimental arm only.
Resting pulse rateQuestionnaires: VAS (fatigue and pain)

Monthly evaluations (E1, E2): At the hospital, for all patients.
Physical capacitiesQuestionnaires: VAS (fatigue and pain)

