**Fig. 1 Fig1:**
[figure not shown]
Study design. A baseline assessment will be performed between the initiation of the OTT and the randomization by the clinician (C0) and the educator (E0). Other assessment will be performed monthly by the clinician (C1, C2, C3) and the educator (E1, E2, E3) at the end of month 1 (M1), M2, and M3, respectively. The different assessments will be performed at the hospital

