### Interventions

#### Experimental arm (SPEP): program A

All participants in the experimental arm will have to start the SPEP session within 15 days following the initiation of the oral targeted therapy.

This program will last 3 months with a total of 12 SPEP sessions (one weekly) plus 24 non-supervised exercise sessions (twice a week). An expert coordinator coach has elaborated three levels of difficulties for this program.

The home-based SPEP sessions are composed of two dimensions: development of the musculoskeletal strength and patients’ endurance (muscular reinforcement of the cardiorespiratory system). These sessions will be supervised by a coach (trained physical educator or physiotherapist) specifically trained for this study, with respect to the pathology and the clinical study. Before each SPEP session, using a visual analogic scale, the coach will determine the patient’s level of fatigue to adjust the intensity, the repetition, and the speed of execution of the exercises proposed during the 60-min session. The coach will report the information of duration and intensity of the sessions in a standardized document.

Between each SPEP session, patients will follow two non-supervised exercise sessions (planned with the coach) consisting of a minimum of 30 min and maximum of 60 min of walk, running, or biking, depending on the patient’s level of fatigue (estimated by patients themselves). For these non-supervised sessions, the coach will provide patient with a heart rate monitor (connected watch) and a dedicated booklet containing personalized physical activity recommendations.

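### Follow-up is timed from programme start in the experimental arm but from randomisation in control, and the 3-month visit carrying the co-primary scores has no stated time origin

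*Protocol article*

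**What the plan says.** Under Interventional visits, the two monthly visits are due at "1 month ±3 days from SPEP initiation [experimental arm] or randomization [control arm" and "2 months ±3 days from SPEP initiation [experimental arm] or randomization [control arm". Table 1 repeats the rule at 6 months. Note h places the body-composition scan at "6 months after initiation of the physical activity for the SPEP group and 6 months after randomization for the standard group", and note l places the tumour evaluation at "6 months ±15 days from SPEP initiation [Arm A] or randomization [Arm B".

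Other time points are anchored differently:

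- **Baseline** (Inclusion visit): done before randomisation in both arms.
- **PFS** (Secondary outcomes): "Progression free survival is defined as the time from randomization to date of disease progression or death of any cause", in both arms.
- **Month 3** (C3/E3, End of study visit): assessments are listed but no origin or window is given. The Fig. 1 legend says only that the monthly assessments fall "at the end of month 1 (M1), M2, and M3, respectively", and the Primary outcome section says only that scores are taken after 3 months.

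Two limits bound the gap between randomisation and programme start. Experimental-arm patients must "start the SPEP session within 15 days following the initiation of the oral targeted therapy". The Randomization section sets the same 15-day limit, from the same starting point, for randomisation itself.

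**The concern.** Time zero depends on the arm. In control it is randomisation. In the experimental arm it is a later event that cannot happen until the patient has been allocated. The offset is therefore zero or positive and exists in one arm only. A symmetric window of ±3 or ±15 days adds scatter around each target date but does not bring the two targets together.

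Two comparisons could be affected. If the month 3 visit follows the same rule, the co-primary scores are compared at slightly different times since randomisation and since the start of oral targeted therapy. The Background describes fatigue as an early side effect of that therapy, so time on treatment may matter. The t-test at 3 months, and the repeated-measures analysis that takes the baseline score into account, are not described as allowing for elapsed time. For PFS, the clock starts at randomisation in both arms but the 6-month evaluation is scheduled later in one. A progression found at that evaluation is then dated later in the experimental arm with no true effect.

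**Working it through.** **The plan's own figure.** Inputs from Sample size and Randomization: difference 2.5 with SD 6.5 (FACT-F) or 5 with SD 13 (physical well-being), two-sided alpha 2.5%, power 80%, allocation 2:1, 5% loss.

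- Control arm: n = (1 + 1/2) × (2.241 + 0.842)² × (6.5/2.5)² = 1.5 × 9.505 × 6.76 = 96.4, so 97.
- Total: 97 + 194 = 291, and 291/0.95 = 306.3, so 307.

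This is within 3% of the stated 312. The point does not turn on this figure, and the fix does not change it.

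**Size of the offset.** Offset = programme start minus randomisation. Both must fall on days 0 to 15 after the start of oral targeted therapy, and programme start cannot come first.

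- Minimum: 0 days.
- Maximum: 15 days, only if randomisation is on day 0 and the programme starts on day 15. This is 15/91 = 16% of a 3-month interval.
- Average (assumption, since the documents give no gap): randomisation uniform over days 0 to 15 and programme start uniform over the days left. The mean is (15/2)/2 = 3.75 days. The share above the 3-day half-window is (12 − 3 ln 5)/15 = 48%.

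**FACT-F, if month 3 follows the split rule.** Spurious difference = monthly drift × gap/30.4. The drift is an assumption; the documents give none.

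| Drift (points/month) | Gap 3.75 days | Gap 15 days for every patient |
|---|---|---|
| 0.5 | 0.06 | 0.25 |
| 1 | 0.12 | 0.49 |
| 2 | 0.25 | 0.99 |

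At 1 point per month this is 4.9% of the 2.5-point target for the average gap, and 19.7% at the extreme.

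**Effect on the FACT-F test.** With 312 randomised and 5% loss, the arms hold 98.8 and 197.6 patients. The standard error is 6.5 × √(1/98.8 + 1/197.6) = 0.80, and power = Φ((2.5 − b)/0.80 − 2.241), where b is the bias against the programme.

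- b = 0: 81%.
- b = 0.12: 77%.
- b = 0.49: 60%.

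If there is no true effect, the two-sided rejection rate rises from 2.5% to 2.7% at b = 0.12 and to 5.4% at b = 0.49, whichever way the drift runs.

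**PFS, as a ceiling only.** If every event were delayed by the full offset, the ratio of apparent medians would be m/(m + gap/30.4). For assumed medians of 6 to 12 months this is 0.98 to 0.99 at 3.75 days, and 0.92 to 0.96 at 15 days. The real effect must be smaller. Only the 6-month tumour evaluation has a stated split origin, later ones follow centre practice (Table 1, notes a and l), and dates of death do not depend on scan dates. Table 1 also lists a tumour evaluation at month 3, but with no stated origin, so it is not counted here.

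**The case against.** Much can be said on the other side.

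- **Month 3.** A reader might infer that the protocol schedules the primary endpoint later in the experimental arm. It does not say so; no origin is given for C3/E3. The inference is reasonable, because months 1, 2 and 6 all use the split and the programme runs 3 months from its start, but it remains an inference. This stands.
- **Size.** A reader might take 15 days as the typical shift. It needs randomisation on the first possible day and programme start on the last. Later randomisation leaves less room. This stands.
- **Drift.** What matters is the slope of fatigue near 3 months, not its early onset. If fatigue sets in early and then levels off, the slope could be near zero. The documents show no slope, so the direction of any bias is unknown. This stands.
- **PFS.** A reader might turn a delay of 7 to 15 days at a 9-month median (274 days) into an apparent hazard ratio of 274/281 = 0.975 to 274/289 = 0.948. That needs every event to be delayed, which the visit schedule does not support. This stands.
- **The two 15-day limits.** A reader might call them contradictory. Both can be met, so they are not; they are only tight when randomisation is late.
- **Design intent.** Counting from programme start places the assessment at the end of the programme. That is a real reason at months 1 to 3, but it gives little support to a split origin for a tumour evaluation that feeds PFS.

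None of this removes the arm-specific origin that the text states for months 1, 2 and 6.

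**Conclusion.** The concern holds in a limited form. The split origin is explicit for months 1 and 2 and for the 6-month scan and tumour evaluation, and it is inferred for month 3. The offset runs one way: 0 to 15 days as written, and about 4 days on average under uniform dates.

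For FACT-F the likely bias is small and of unknown direction. It is about 0.1 points at an assumed drift of 1 point per month, and at most about 0.5 points at that drift if every patient had a 15-day gap. For PFS there is a small bias favouring the programme, confined to progressions detected at the 6-month evaluation. The documents support neither a stated shift of the primary endpoint nor a hazard ratio of about 0.95 to 0.97 arising from timing alone.

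It should still be corrected: the bias is avoidable, it affects one arm only, and removing it is cheap.

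**What to change.** Time the 6-month scan and tumour evaluation, and C1 to C3 and E1 to E3 with their questionnaires, from randomisation in both arms with identical windows. State the origin and window for C3/E3 explicitly. By design the offset is then 0 days, and the sample size is unchanged.

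The cost is an amendment to visit timing. At 6 months there is no real downside. At month 3, the visit may fall shortly before the last sessions in patients who start the programme late.

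Recruitment was under way at publication and phase II patients enter the phase III analysis, so some patients will have followed the split schedule. For them, report the days from randomisation to the month 3 questionnaires by arm, and adjust for those days in a sensitivity analysis of the co-primary scores. This needs only visit dates.

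Separately, clarify how the limits in the Randomization section and the experimental-arm section work together. Both run for the same 15 days from the start of oral targeted therapy, which leaves little or no time to start the programme after a late randomisation. If programme start then slips past its limit, the 15-day ceiling on the offset no longer holds.
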